### Enrollment procedure and baseline data collection

Eligible patients are informed about the project by a doctor or nurse in the outpatient clinic.

Patients who have signed the informed consent form are asked to complete a baseline questionnaire. Baseline characteristics of the patient (WHO performance status, diagnosis, age, gender, time of primary diagnosis, cancer stage, marital status, and educational background) are registered. Randomization is subsequently performed by the clinical trial unit using a randomization list from randomizer.org [20]. Patients are randomized 1:1 to the intervention or control group with no further stratification used during randomization. The randomization list is blinded from anyone involved in informing potential study participants.

If a patient does not wish to participate, the reason is noted, if possible, and the following characteristics are registered anonymously; diagnosis, age, gender, WHO performance status, cancer stage, marital status and educational background.

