#### Measurement instruments

All participants complete a questionnaire at baseline and six and 12 weeks after randomization. The questionnaire consists of EORTC QLQ-C30, which is a validated and widely used questionnaire for assessing symptoms and QoL in cancer patients [23], and Hospital Anxiety and Depression Scale (HADS), which is also validated and often used for screening and assessment of symptoms of anxiety and depression in palliative care, oncology, and other fields of research [24].

The EORTC QLQ-C30 consists of 30 items in 15 scales. In the present study additional items measuring role functioning, cognitive functioning, social functioning, dyspnea, pain, fatigue, insomnia, appetite loss, nausea/vomiting and constipation were added to the questionnaire to expand these scales to at least four items in each scale. The extra items were taken from the item banks developed for computer-adaptive testing of the EORTC QLQ-C30 dimensions [25–28]. The international clinical validation of the item banks is ongoing.

At baseline the patient prioritizes one “primary problem” from a list of 12 categories of “primary problems” corresponding to 12 of the 15 scales of EORTC QLQ-C30, or “none of the above” (Table 5). At six and 12-weeks follow-up the patient is asked whether he/she has received help with the “primary problem” (yes/no) and if yes, whether the help was “insufficient”, “partly sufficient” or “sufficient”.

**Table 5 Tab5:** List of possible “primary problems” the study participants to choose from

“Primary problem”	Corresponding outcome measure in EORTC QLQ-C30
Limitations in physical functioning	Physical function scale
Limitations in work and daily activities	Role function scale
Limitations in social life	Social function scale
Problems with memory and concentration	Cognitive function scale
Emotional problems (worry, irritation, depression, tension)	Emotional function scale
Fatigue (tiredness and weakness)	Fatigue scale
Pain	Pain scale
Breathlessness	Dyspnea item
Loss of appetite	Loss of appetite item
Nausea	Nausea and vomiting scale
Constipation	Constipation scale
Trouble sleeping	Insomnia item
None of the above	

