### Statistical analysis and sample size calculation

#### Sample size estimation

Data from other studies using EORTC QLQ-C30 suggest a standard deviation of less than 25 for a difference between the repeated measurements, and a group difference of 10 for clinical relevance [31].

With a risk of type I error of 0.05 and type II error of 0.10, 133 patients are required in each arm. In order to allow for a dropout rate of approximately 10% each arm will enroll 150 patients for a total of 300 patients.

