### Plan of analysis

#### Questionnaire data

Analyses will be made using the statistical package STATA, latest version (StataCorp, Texas, USA). The primary analysis will be based on the intention-to-treat principle. If the proportion of lacking answers is higher than 5%, we will use multiple imputations in the primary analysis with the following variables: age, gender, diagnosis, cancer stage, and WHO performance score. The questionnaire data will be transformed according to their respective scoring manuals [32, 24].

Multiple regressions will be applied, since despite the randomized design there may be imbalance between the two arms. We will adjust for “the primary problem” and WHO performance score.

Wilcoxon and Chi2 will be used to investigate whether there are differences between the two groups in relation to the following variables that may be of prognostic importance: gender, age, cancer stage, primary diagnosis, marital status, and educational background. If a significant group difference is found, the respective variable will be included in a sensitivity analysis.

In the analyses we combine the data from the three questionnaires by constructing an AUC using a weighted average of the change from baseline to the 6 and 12-week follow-up. A model for longitudinal data and repeated measurements in the multivariate analysis is applied as a subsequent sensitivity analysis.

Since the primary outcome measure “the primary problem” consists of 13 possible choices, we will also perform separate analyses of patients with the same primary problem.

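### Separate analyses within each of up to 13 primary-problem groups are imprecise and do not test whether the effect differs by problem; a treatment-by-problem interaction in the all-patient model would

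*Protocol article*

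**What the plan says.** All references are to the protocol article.

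- **Measurement instruments.** At baseline each patient picks one problem "from a list of 12 categories of “primary problems” corresponding to 12 of the 15 scales of EORTC QLQ-C30". A patient may also decline all twelve and is then scored on the global health status/QoL scale, so there are 13 groups.
- **Plan of analysis, Questionnaire data.** The primary analysis is a regression on all patients, adjusted for primary problem and WHO performance score. The section then turns to the number of options ("Since the primary outcome measure “the primary problem” consists of 13 possible choices"). Its response to this is stated in the same sentence: "we will also perform separate analyses of patients with the same primary problem". No treatment-by-problem term is named.
- **Sample size estimation.** The trial is sized for the overall comparison only: "With a risk of type I error of 0.05 and type II error of 0.10, 133 patients are required in each arm". This rests on data that "suggest a standard deviation of less than 25 for a difference between the repeated measurements". The target effect is "a group difference of 10 for clinical relevance".
- **Enrollment procedure and baseline data collection.** "Patients are randomized 1:1 to the intervention or control group with no further stratification used during randomization", so the arms need not be balanced within a problem.

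**The concern.** Whether the programme helps some problems more than others is a natural question when the outcome is assembled from 13 different scales. Thirteen separate comparisons do not answer it. A significant result for one problem and a non-significant result for another is not evidence that the two effects differ; small groups produce that pattern even when the effect is the same everywhere. In the all-patient regression, primary problem enters as a main effect, which lets the mean change vary by problem but holds the treatment effect constant. Neither stated analysis therefore tests for a difference in effect.

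The patient-chosen problem is presented in the Discussion as a novel feature of the trial, so by-problem results could be read as showing which problems the programme helps. They would be a weak basis for that.

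**Working it through.** **Inputs.** Difference 10 points; SD 25 (given as an upper bound); type I error 0.05; power 90%; 133 evaluable per arm; 150 enrolled per arm; 13 groups. All come from the sections cited above. The article does not say whether the test is one- or two-sided.

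**Reproducing the plan's figure.** Two-sided normal approximation: n = 2 × (1.960 + 1.282)² × (25/10)² = 131.3, so 132 per arm. The noncentral t gives exactly 133. A one-sided test gives 108 and does not match. For dropout, 133/0.90 = 147.8, so 148, rounded up to 150. The design basis is confirmed and is used below.

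**Precision at an equal split (assumed, with equal arms in each group).**

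| Patients | Per arm per group | Power (t) | Power (normal) | 95% half-width |
|---|---|---|---|---|
| 266 | 266/13/2 = 10.2 | 13.8% | 14.6% | 23.2 |
| 300 | 300/13/2 = 11.5 | 15.1% | 15.9% | 21.6 |

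Half-width = t × 25 × √(2/m), with m patients per arm. It is more than twice the 10-point difference.

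**Range over group size (SD 25, noncentral t).**

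| Patients in group | 10 | 20 | 40 | 60 | 100 |
|---|---|---|---|---|---|
| Power | 9% | 14% | 23% | 33% | 51% |

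For 80% power a group needs about 200 patients: 2 × (1.960 + 0.842)² × 6.25 = 98.1, so 99 per arm or 198 in total by the normal approximation, and about 200 by the t. Of 266 evaluable patients that is about 75% (200/266), so at most one problem could reach it.

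**Range over SD (equal split, 266 patients).** SD 20 gives 19–20% power; SD 15 gives 30–33% (t to normal).

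**Why the separate results do not show heterogeneity.** Suppose the true effect is 10 points for every problem. At an equal split with 266 patients, the expected number of significant groups is 13 × 0.138 = 1.8. A table with about two significant problems and eleven non-significant ones is then the typical result of a uniform effect.

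**False positives across the set.** Suppose all 13 groups are tested at two-sided 5%, unadjusted, with no effect in any. The groups contain different patients, so independence is reasonable.

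- At least one significant in either direction: 1 − 0.95¹³ = 48.7%.
- At least one favouring the intervention: 1 − 0.975¹³ = 28%.

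**The case against.** The strongest reply is that these analyses are supplementary. They follow a primary analysis on all patients, the trial is sized for that analysis alone, and showing results by component is ordinary transparency for a composite of 13 scales. The article does not say that each group will be tested at 5%, that groups will be compared, or that any problem will be called responsive. Multiplicity rules, minimum group sizes and an exploratory label are details that a statistical analysis plan or full protocol may hold, and neither is shown.

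Most of this stands. The absence of those details is not a fault here, and reporting by problem is worth keeping. What remains is that the article fixes separate analyses as its approach to the 13 choices, and that approach cannot show whether effects differ. This holds whatever the group sizes, SD or significance level.

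Four stronger readings are tempting, and the documents do not support them:

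- *Every group has 14–15% power.* This needs 13 equal groups. Patients choose freely and no distribution is given, so a popular problem will do better and a rare one worse. The SD is stated only as below 25, and the outcome is an adjusted average of two follow-ups, so 25 is a cautious value.
- *A false finding of benefit for some problem is as likely as not.* The 49% counts results in either direction, over the whole set and not per test, and assumes no effect anywhere. The figure for a false benefit is 28%, under the same conditions.
- *The trial's type I error is compromised.* The by-problem analyses do not enter the primary comparison.
- *The by-problem results should be dropped or replaced by shrunken estimates.* Pooling across problems assumes that effects on quite different scales are exchangeable. That is debatable, and separate estimates do not need it.

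**Conclusion.** The point holds as one about method and precision in a supplementary analysis. Separate within-group comparisons, with primary problem only a main effect in the overall model, do not test whether the effect of the programme differs by problem. They are also imprecise. Power to detect 10 points is about 14–15% per group at an assumed equal split with SD 25, about 9–51% for groups of 10 to 100 patients, and about 19–33% at an equal split if the SD is 15–20. All these figures assume equal arms within each group; unstratified randomization will give some imbalance, which lowers power further. The 49% and 28% error figures are conditional on 13 unadjusted two-sided 5% tests and no true effect. The sample size and the primary comparison are not in question.

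**What to change.** 1. In the all-patient regression, align the scales so that a positive change means improvement for every problem, and add a treatment-by-primary-problem interaction. Make its overall test (12 degrees of freedom if all 13 groups contain patients from both arms) the basis for any statement that the effect differs by problem.
2. Keep the problem-specific results, as estimates with 95% intervals and the number of patients per arm, labelled exploratory and without separate significance claims.
3. Optionally, add partially pooled estimates next to the separate ones, stating the exchangeability assumption.

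The cost is a change of analysis wording and a few lines of code; no further data are needed. The downside is that the interaction test uses the same small groups and has limited power itself. A non-significant interaction must not be reported as showing equal effects, and the intervals should carry the interpretation.

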### Survival

Survival will be described by Kaplan-Meier plots. Patients still alive three months after final data collection will be censored as of that date. A Cox regression model will also be applied controlling for the same variables as in the questionnaire data analysis.

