## Methods/design

### Study design

The study is a phase III, controlled, randomized trial with 300 patients allocated 1:1 to an intervention or a control group at the Department of Oncology, Vejle Hospital. The department offers treatment to adult patients with pulmonary, breast, prostate, colorectal, anal and biliary tract cancer, as well as cancers of the female reproductive organs. On a yearly basis there are around 57,000 outpatient visits and 23,000 radiotherapy fractions and 9300 chemotherapy treatments are administered. Geographically, the patients have up to 1½ hours of transport time by car to the hospital.

Newly diagnosed advanced cancer patients initiating oncologic treatment who consent to participate will be randomized to an individually tailored palliative rehabilitation program alongside their standard oncology care (disease specific treatment) or to standard oncology care alone. Study measures and timepoints can be seen in Fig. 1.

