### Economic consequences

Data on the number and length of hospital admissions and treatments, visits to outpatient clinics, emergency rooms, and general practitioners are applied in the evaluation of economic consequences of the intervention. The calculation includes the period from enrolment until three months after final data collection. The data are available from the Danish National Patient Registry [33] and the costs of the different services are obtainable through the Danish Health Authority.

Multivariate analysis is used to compare the two groups controlling for the same variables as in the questionnaire data analysis.

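### The Cox model inherits the questionnaire covariates and so leaves diagnosis and cancer stage out of the main survival analysis; if the intervention does affect survival, this costs precision of inference at no gain

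*Protocol article*

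**What the plan says.** The Survival section describes Kaplan-Meier plots and then a regression: "A Cox regression model will also be applied controlling for the same variables as in the questionnaire data analysis". The set it refers to is given under Questionnaire data: "We will adjust for “the primary problem” and WHO performance score". The primary problem is a categorical variable that "consists of 13 possible choices", hence 12 model terms.

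The same section lists "variables that may be of prognostic importance: gender, age, cancer stage, primary diagnosis, marital status, and educational background". These are to be compared between arms by significance tests, with this consequence: "If a significant group difference is found, the respective variable will be included in a sensitivity analysis". Diagnosis and stage also appear among the multiple-imputation variables, but that does not adjust the treatment effect.

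Three other places bear on the point. Study design says the department treats "adult patients with pulmonary, breast, prostate, colorectal, anal and biliary tract cancer, as well as cancers of the female reproductive organs". Enrollment procedure and baseline data collection says that diagnosis and stage are recorded for every patient, and that allocation is 1:1 without stratification. Study objectives names survival as a secondary objective.

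**The concern.** The covariate set was chosen for a symptom score. Carried over to survival, it adjusts for which symptom the patient ranked first, but not for tumour type or stage. Yet the plan draws on a department that treats cancers from lung and biliary tract to breast and prostate, and it names diagnosis and stage as potentially prognostic.

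The hazard ratio is non-collapsible. If a strong prognostic factor is left out of a Cox model and treatment truly works, the treatment coefficient shrinks towards zero even when the arms are perfectly balanced. Its standard error hardly changes, so power falls. A real survival benefit or harm could be understated or missed although the data needed to avoid this have already been collected.

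**Working it through.** **The plan's own figure.** The only sample size calculation is for the questionnaire outcome: SD 25, difference 10, type I error 0.05, power 0.90. Two-sided normal formula: n = 2 × (1.960 + 1.282)² × 25² / 10² ≈ 131.3, so 132 per arm; the t-based version gives the stated 133. With 10% dropout, 133 / 0.90 = 147.8, in line with 150. So that figure reproduces. No hazard ratio, event target or power is given for survival.

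**The trigger.** The plan does not state a level for the baseline tests; take 5%. Under randomization each test is then significant about 5% of the time, however prognostic the variable. For two variables, treated as independent, the chance that neither is flagged is 0.95² = 0.9025. In about 90% of trials both stay out of even the sensitivity analysis.

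**The effect on the Cox model.** A simulation of 2,000 trials per scenario compared
- the stated model: treatment (1 term), primary problem (12), WHO score (2), 15 terms in all;
- the extended model: the same plus diagnosis (5 terms, anal grouped with colorectal) and stage (1), 21 terms in all.

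From the documents: 300 patients, 1:1, unstratified, 13 primary-problem categories, seven tumour types. Assumed, because the documents are silent: conditional hazard ratio 0.70; exponential survival with reference median 14 months; censoring uniform over 6 to 38 months (about 170 events); tumour shares; WHO score prognostic with log hazard ratio 0.5 per level; primary problem not prognostic and unrelated to diagnosis; and the strength of diagnosis (SD of its log hazard) and stage (log hazard ratio), which was varied.

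The average hazard ratio is the exponential of the mean coefficient. Power is the share of trials with |coefficient / SE| > 1.96.

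| Strength (diagnosis SD; stage log HR) | HR stated | HR extended | Power stated | Power extended |
|---|---|---|---|---|
| None (0; 0) | 0.692 | 0.686 | 63.3% | 63.5% |
| Weak (0.3; 0.3) | 0.708 | 0.693 | 57.8% | 60.8% |
| Moderate (0.5; 0.5) | 0.714 | 0.682 | 55.5% | 64.7% |
| Strong (0.8; 0.7) | 0.749 | 0.684 | 43.6% | 62.7% |

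**Check by hand, strong case.** Power ≈ Φ(|ln HR| / SE − 1.96).
- Stated model, SE 0.160: |ln 0.749| = 0.289; 0.289 / 0.160 = 1.81; Φ(−0.15) ≈ 44%.
- Extended model, SE 0.166: |ln 0.684| = 0.380; 0.380 / 0.166 = 2.29; Φ(0.33) ≈ 63%.

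The SEs are almost equal, so the loss comes from the shift in the estimate.

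**Small-sample drift.** Even with nothing prognostic omitted, both models average slightly below 0.70 (0.692 and 0.686), as many terms on about 170 events tend to produce. About 0.006 of each gap in the table is therefore drift from the extra terms rather than attenuation. This matters mainly in the weak case, where the whole gap is 0.015.

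**No true effect.** At hazard ratio 1.0 both models average 1.00 to 1.01. Rejection rates are 5.4% to 7.0% for the stated model and 5.7% to 6.9% for the extended one.

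**Stratifying instead.** Stratification by diagnosis and stage gives power of 57.6%, 61.4% and 60.2% in the weak, moderate and strong cases: no gain over the stated model in the weak case, and less than covariate adjustment in all three.

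**The case against.** The best defence has four parts.

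1. The stated analysis is a valid test. With no effect on survival, the type I error is essentially the same in both models. Attenuated only means different from the ratio within diagnosis and stage, and only if an effect exists. This stands. A reader might infer a biased comparison or false-positive survival claims; neither follows. Chance imbalance in tumour mix adds noise to a single trial's estimate, not systematic bias.

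2. The plan has a safeguard, since an unbalanced variable goes into a sensitivity analysis, and "A Cox regression model will also be applied controlling for the same variables as in the questionnaire data analysis" can be read to import that step. This stands only in part: the step responds to imbalance rather than prognostic strength, and it does not change the main model.

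3. The size is assumed. The documents give no survival rates, and the list of cancers describes the department, not the enrolled case mix. Enrolment is confined to non-resectable disease, which may narrow the spread in stage. WHO score or primary problem could also carry some information on tumour type or stage, which the simulation excludes and which would narrow the gap. All of this stands and is why a range is given.

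4. Survival is secondary and no power is claimed for it. This stands and limits the weight of the point.

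Two further inferences are tempting. One is that adjusting for primary problem does harm: with no other prognostic factor omitted, the stated model with all 12 terms averages 0.692, so those terms alone do not pull the estimate towards 1. The other is that the cost comparison shares the fault, because "Multivariate analysis is used to compare the two groups controlling for the same variables as in the questionnaire data analysis". The economic section names no Cox model, non-collapsibility of the hazard ratio need not carry over (for example to a linear cost model), and nothing was calculated for it. No claim is made there.

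**Conclusion.** The point holds as one of efficiency and estimation in a secondary analysis. The protocol positively fixes a survival covariate set that omits two variables it regards as possibly prognostic, and the route by which they could return is unrelated to prognostic strength.

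On the assumptions above, the omission costs about 3, 9 or 19 percentage points of power for weak, moderate or strong prognostic effects, with average hazard ratios of 0.71, 0.71 and 0.75 against 0.69, 0.68 and 0.68. The weak-case difference is small enough to disregard by itself. If diagnosis and stage carry no prognostic information, including them changes power by 0.2 points. Gain in the plausible cases with practically no loss in the other is what makes the change worthwhile. A single power loss cannot be quoted as fact from these documents. The validity of the test and the primary conclusion are untouched.

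**What to change.** In the Survival section, replace the cross-reference to the questionnaire covariates with a list for this model: primary diagnosis (rare tumour types grouped), cancer stage and WHO performance score, all as covariates and all included whatever the baseline tests show. Define the diagnosis grouping in advance. The primary-problem terms were chosen for the questionnaire outcome and are not needed here; they may be left out, or kept with a reason.

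The cost is about one sentence and a few more model terms (six in the set-up above). No new data are needed, since the variables are recorded at enrolment. The Time plan reports 68% recruitment with the analyses still ahead, so the change could be made before any comparative survival result is seen.
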